## Abstract

Cognitive frailty (CF) is a heterogeneous syndrome that is becoming one of the most serious health problems as the world’s population age is increasing. Elucidating its biological mechanisms as well as prevention and treatments is becoming increasingly significant, particularly in view of the associated health costs. We presented the study protocol of a research project funded by the Italian Ministry of Health (grant number RF-2016-02363298) aiming to investigate the cognitive and neuropsychological effects of a 5-week treatment with therapy based on the regenerative properties of ozone (O_3_) in a cohort of subjects stratified according to CF scores. We also studied the potential effects of O_3_ on blood-based biomarkers indicative of specific biological systems that may be altered in CF. Seventy-five older persons were recruited and randomly assigned to receive the active treatment (150 cc of oxygen-O_2_-O_3_ mixture at the concentration of 30 µg of O_3_ per cc of O_2_), O_2_, or the placebo (air) for 5 weeks. The main endpoints were the change in the scores of clinical scales from baseline (T0) to weeks 3 (T3), 9 (T9), and 15 (T15) after treatment and the change in biomarker levels resulting from transcriptomics, proteomics, and metabolomic patterns at the same times. The positive results from this study could have important clinical implications.

## 1. Introduction

Frailty is a multidimensional geriatric syndrome characterized by increased vulnerability to stressors as a result of the reduced functional capacity of different physiological systems [1,2,3,4]. Consequently, adults with frailty may be subject to frequent falls, may be disabled and immobile, may have a lower-quality life, and can require hospitalizations [5]. It has been estimated that the prevalence of frailty ranges from 4.0 to 59.1%, detected among community-dwelling older individuals aged 65 and older [6,7]. 

In addition to frailty in a general sense, there is another field that deserves attention in the context of aging, which is that of cognitive impairment. Frailty and cognitive impairment co-occur together and are complicatedly related [8], determining significant disability, reduced quality of life, and higher morbi-mortality [9]. In April 2013, the International Academy of Nutrition and Aging (IANA) and the International Association of Gerontology and Geriatrics (IAGG) agreed that “cognitive frailty” (CF) is a simultaneous state of both cognitive impairment (clinical dementia rating [CDR] = 0.5) and physical frailty (frailty phenotype) in older individuals without a definite diagnosis of dementia independent of other frailty dimensions (e.g., social, psychological and oral frailty) [10]. Although the definitions and assessments of CF have undergone some changes over time, older adults with both physical frailty and cognitive impairment are shown to be at higher risk of adverse health outcomes, such as death, disability, and hospitalization, than those with either condition alone [11,12,13]. Physical frailty can accelerate cognitive impairment as well as increase the risk of mild cognitive impairment (MCI) and dementia [14,15]. Particularly, a specific network named the salience network (SN) is functionally impaired in MCI or dementia patients [16,17]. The SN nodes (right anterior insula (RAI), left anterior insula (LAI), and combined left/right anterior cingulate cortex (ACC)) make up a key cortical network that detects and integrates responses to salient stimuli. AI regions of SN are functionally involved in coordinating activities in many cognitive processes, such as the reorientation of attention and switching among cognitive resources; ACC is primarily implicated in increased cognitive controls and conflict monitoring and regulates neural activities in association with AI regions during difficult tasks. In general, SN has been implicated in modulating the switch between the internally directed cognition of the default mode network (DMN) and the externally directed cognition of the central executive network (CEN).

Nine percent is the estimated prevalence of CF in adults aged 65 years and older, and it is common in older women living in the community [18].

The underlying molecular mechanisms of CF remain unclear. However, based on the close association seen between physical frailty and cognitive impairment, several review articles suggest that impaired hypothalamic–pituitary axis stress responses, energy homeostasis and mitochondrial dysfunctions, endocrine dysregulation, oxidative stress, nutritional and metabolomic factors alterations, gut dysbiosis, and vascular risk factors and diseases represent the potential underlying common mechanisms among these conditions [19]. Importantly, the phenotype of frailty has also been associated with underlying inflammatory mechanisms. A recent review [20] supported the potential role of some biomarkers such as, for instance, C-reactive protein (CRP) as an inflammatory marker and as a prognostic index in this syndrome.

For these multifaced underlying causes, accumulating evidence indicates the need for comprehensive geriatric assessment that helps to better characterize the CF etiopathogenesis, but also to develop, at the same time, new individualized mono-domain interventions to prevent adverse health outcomes for older adults with CF.

Since 1840, from its discovery, ozone (O_3_) and, consequently, oxygen (O_2_)-O_3_ therapy has expanded into the medical field, giving rise to compelling research in the recent decades which validates its clinical value [21]. Several papers [22,23,24] emphasized its relevant medical features, such as virucidal and bactericidal effects, inflammatory modulation, and circulatory stimulation, with considerable applications in several medical fields [25]. O_3_ is considered one of the most powerful oxidizing molecules in nature [26]. Indeed, its function is strictly associated with its power to directly interact with lipoproteins, phospholipids, viral capsids, and bacteria envelopes. Particular attention was recently paid to further specific O_3_ activities related to the cellular and humoral immune system which contribute to the proliferation of immunocompetent cells and the synthesis of immunoglobulins as well as biologically active substances (interleukins, leukotrienes, and prostaglandins). In this sense, O_3_ also seems to activate macrophage function and increase the sensitivity of microorganisms to phagocytosis. Finally, it has also been reported that O_3_ can interact with blood cells or other elements of the circulatory system, which would have beneficial properties to O_2_ metabolism, the antioxidant defense system, cellular energy, and microcirculation [26].

If, on the one hand, experimental evidence provides a solid preclinical rationale for the application of O_2_-O_3_ therapy to improve cognitive profiles in aging [27,28,29,30], clinical studies supporting its potential beneficial effects on cognition in humans are not available.

Here, we presented the study protocol of a research project funded by the Italian Ministry of Health (grant number RF-2016-02363298). The main aims of this research project are (1) to clarify the potential cognitive and neuropsychological effects of a 5-week treatment with O_2_-O_3_ therapy on older adults with frailty; (2) to elucidate the potential effects of this therapy on blood-based biomarkers associated with transcriptomics, proteomics, and metabolomics patterns. We describe the protocol study by dividing the Material and Methods section into two parts, where we specify what steps have been performed (PART 1) and what steps will need to be performed (PART 2). 

## 2. Materials and Methods

The study is a randomized, double-blind, placebo-controlled, 5-week trial to assess the cognitive, neuropsychological, and biological effects of O_2_-O_3_ therapy on 75 older adults stratified according to CF scores. The study is being performed at the IRCCS Centro San Giovanni di Dio Fatebenefratelli, Brescia, Italy. In Table 1, we show the activities and timelines of the study.

As this is an ongoing trial, we divided this section into two parts where we specify what steps have been performed (PART 1) and what steps will need to be performed (PART 2).

### 2.1. PART 1

#### 2.1.1. Trial Design and Setting

Participants have been recruited among those who have already had access to the Translational Memory Clinic of the IRCCS Centro San Giovanni di Dio Fatebenefratelli, but also by several methods, including advertisements in local newspapers, flyers located at our institute, and meetings in different cultural centers for the elderly. During the clinical trial for screening, we facilitated retention by regular contact and reminders in appointments and in the testing sessions.

#### 2.1.2. Ethics Approval

The protocol (version 3.0) was approved by the local ethical committee, the Ethics Committee of the IRCCS Centro San Giovanni di Dio Fatebenefratelli (rif. Parere 40-2018). At the time of face-to-face screening, all participants provided written informed consent to the study protocol to a member of the research team. The research was carried out in accordance with the International Conference on Harmonization of Good Clinical Practice (GCP/ICH) guidelines and was conducted in line with the principles of the Declaration of Helsinki.

#### 2.1.3. Inclusion and Exclusion Criteria

Inclusion and exclusion criteria have been applied to this trial. The inclusion criteria were that the subjects had to have an age range of 60–85; a diagnosis of amnesic or non-amnesic cognitive disorder, reported by the subjects themselves or by family members; an MMSE score ≥ 24/30; pharmacological therapy for the treatment of stable cognitive or behavioral disorders for at least 3 months at the time of enrolment; no presence of dementia or ascertained Alzheimer’s disease detected by the most advanced diagnostic techniques; function intact, or functional reduction not related to the cognitive problem. We excluded subjects who were affected by disabling vision or hearing impairments; affected by known psychosis or psychiatric illness, alcohol or drug abuse; affected by uncontrolled hyperthyroidism or by Glucose-6-Phostate Dehydrogenase Deficiency (G6PD)-Favism; and those who considered the methodology for rectal insufflation invasive. 

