## 3. Discussion

This article presents the rationale and the materials/methodologies of this ongoing pilot clinical trial that has the aim of analyzing the cognitive and biological effects of O_2_-O_3_ therapy on the clinical/neuropsychological and molecular patterns in older adults with CF. This study protocol is a research project funded by the Italian Ministry of Health, grant number RF-2016-02363298. Molecular analyses and their correlations with clinical and neuropsychological profiles and with different treatments with O_2_-O_3_ therapy are currently ongoing.

Currently, specific treatments are not completely available for elderly individuals affected by CF, subjects who are potentially at risk of developing cognitive impairment and dementia. Consequently, the implementation of further potential strategic interventions may represent a useful approach to promote cognitive health and ultimately prevent cognitive decline.

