By using a certificated O_3_ generator device, a gas mixture of O_2_-O_3_ obtained from the modification of medical-grade O_2_ is employed in the medical setting [41]. The therapeutic range of O_3_ has been precisely calculated, starting from the basic mechanisms of action of O_3_ in blood, and it has been found to be 10–80 μg/mL of O_3_ in blood [42]. Different and main routes of application with relative concentrations of O_3_ have been widely described by Schwart-Tapia et al. [42]. The side effects are minimal: the World Federation of Ozone therapy (WFOT) estimates the incidence of complications at 0.0007%. Moreover, given that most patients report a feeling of wellness and euphoria during the cycle of the treatment, O_3_ treatment is perfectly tolerated, and this explains why the compliance of patients remains excellent throughout the years.

To assess the frailty/CF, we used IFI as well as SHARE-FIt scales, along with CDR scores.

As reported in Sugimoto [19], there are some important issues that lead to difficulty in adapting the CF concept to clinical practice. Indeed, many studies use varied CF models and assessment tools with varied definitions of CF, making the comparison of findings across studies challenging. Therefore, a valid operational definition and an assessment tool that detect older adults at risk for reversible conditions could need to be established. Another challenge is represented by the lack of an appropriate tool for the evaluation of cognitive impairment. In this direction, we have enriched our clinical valuations by implementing a complete battery of neuropsychological tests which have been used in our trial.

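### Neither entry to the trial nor its cognitive-frailty strata require physical frailty or CDR 0.5, so results could not be attributed to cognitive frailty as the Introduction defines it

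*Protocol article*

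**What the plan says.** **Definition.** Section 1 (Introduction) reports a 2013 consensus that describes CF in these words: "simultaneous state of both cognitive impairment (clinical dementia rating [CDR] = 0.5) and physical frailty (frailty phenotype) in older individuals". The consensus also rules out people already diagnosed with dementia.

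**Population named.** The first aim in section 1 concerns the effects of "therapy on older adults with frailty". Section 2 describes "75 older adults stratified according to CF scores". Section 3 (Discussion) gives the aim as studying clinical and "molecular patterns in older adults with CF".

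**Entry criteria.** Section 2.1.3 lists age 60 to 85, a cognitive disorder (amnesic or not) reported by the person or a relative, MMSE of at least 24 out of 30, medication stable for three months, no dementia, and "function intact, or functional reduction not related to the cognitive problem".

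**Strata.** Section 2.1.5 forms three levels of CF from tertiles of memory tests, attention tests, MMSE and GDS. The tertiles were set on successive groups of 12 to 16 subjects and used to balance the arms.

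**Assessment.** Section 2.1.4 lists IFI, SHARE-FIt and CDR as the frailty tools. Section 3 states: "To assess the frailty/CF, we used IFI as well as SHARE-FIt scales, along with CDR scores".

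**The concern.** One label covers three different things: a definition that joins a physical and a cognitive component, strata built from cognition and mood alone, and a statement that the condition was assessed with two frailty scales and the CDR. If the label is carried into the results paper, readers will take any treatment effect as an effect in people who have CF. The primary endpoint is change in a frailty score (section 2.1.7), and section 4 expects the data to inform public health planning. What the sample represents therefore bears directly on what the trial can conclude.

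**Working it through.** The plan gives no figure for the share of participants with CF, so there is none to reproduce. The power figures in section 2.1.12 concern a regression of the frailty scales on neuropsychological tests and do not bear on this point. The check is a comparison of texts.

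| Component of the Introduction's definition | Entry criteria (2.1.3) | CF strata (2.1.5) | Measured (2.1.4) |
|---|---|---|---|
| Physical frailty | No threshold on any frailty scale | No IFI, SHARE-FIt or grip strength | Yes: IFI, SHARE-FIt |
| CDR = 0.5 | Reported cognitive disorder and MMSE of at least 24; no CDR value | Cognitive tests and MMSE; no CDR | Yes: CDR |
| No dementia | Required | Not applicable | Yes: CDR |
| (not in the definition) mood | Not used as a score | GDS included | Yes: GDS |

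1. *Entry.* Only the no-dementia component is required in the form in which the definition states it. The cognitive component is approached but not fixed at CDR 0.5, and the physical component is absent. A robust person with CDR 0, a reported cognitive disorder and MMSE 28 meets the listed inclusion criteria if the other entries on the list are satisfied.

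2. *Strata.* Tertiles rank whoever was enrolled. They yield three levels whether everyone, some or no one has CF, so stratum membership does not show that a person has the condition. The strata balance cognition and mood between arms; they were not built to balance baseline frailty.

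3. *Assessment.* The scales named in the Discussion were collected, but the article does not say that they were used to select or stratify anyone. The Discussion also speaks of subjects screened for CF scores, without a cut-off.

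4. *Size.* The only available numbers are the prevalences cited in the Introduction. Expected count = 75 × share:
   - CF, 9% at age 65 and over: 75 × 0.09 = 6.75, about 7.
   - Physical frailty, low end: 75 × 0.040 = 3.0.
   - Physical frailty, high end: 75 × 0.591 = 44.3.

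   Half the sample is 37.5, so the frailty range runs from almost no one to a majority. These are community or general older-population figures, whereas section 2.1.1 recruits partly from a memory clinic and section 2.1.3 selects for cognitive disorder. The figures show that the share cannot be read from the document; they do not estimate it.

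**The case against.** **Definitions of CF vary.** The article says so in sections 1 and 3, and it does not state that the 2013 definition governs entry. That is fair. However, it adopts no other definition that its entry criteria or strata would meet. Its own looser description in section 1 still joins physical frailty to cognitive impairment.

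**The article condenses a fuller protocol.** Section 2.1.2 cites version 3.0, which is not shown, and Figure 1 is missing. A threshold there cannot be ruled out. The point rests on what the article does state: an explicit list of criteria and an explicit recipe for the strata, both at odds with the population it names.

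**No result is claimed yet.** This is correct. The Conclusions speak of at-risk older people and of preventing cognitive deterioration. The problem lies in how the population and aims are labelled, and it can be corrected before results are written.

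A reader might also be tempted by stronger inferences that the documents do not support:
- *That most participants do not have CF.* This would rest on "Nine percent is the estimated prevalence of CF in adults aged 65 years and older", applied to a sample enriched for cognitive disorder. The result is possible but not established.
- *That the function criterion keeps frail people out.* It does not. Its second half admits reduced function from non-cognitive causes. The strata set against the definition are the stronger evidence.
- *That the frailty scores have no room to improve.* No baseline IFI or SHARE-FIt values are given, and section 2.2.2 treats both as continuous, so a floor effect is conjecture.
- *That the randomised comparison is undermined.* Not selecting for CF does not bias the comparison between arms. The limit is on whom the result describes.

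**Conclusion.** The point holds as a mismatch between the population named and the population selected and stratified. As the article stands, results could not be attributed to older adults with CF in the sense of its Introduction, and the tertiles in section 2.1.5 are levels of cognition and mood rather than of CF. Its size in participants is unknown. The conclusion assumes that the list in section 2.1.3 is complete with respect to frailty and CDR, and that the Introduction's definition is the one meant, since no other is offered. It makes no assumption about how many participants are frail.

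**What to change.** 1. Describe the population as adults aged 60 to 85 with a reported cognitive disorder, MMSE of at least 24 and no dementia, not selected for physical frailty. Use that description in the aims and the Discussion. If version 3.0 of the protocol does contain a frailty or CDR criterion, state it in section 2.1.3 instead.
2. Call the strata cognitive/mood tertiles, and reconcile section 2.1.5 with the Discussion's statement on how frailty/CF was assessed.
3. From the baseline CDR, SHARE-FIt and IFI already collected, tabulate by arm how many participants meet the Introduction's definition. The article gives no cut-off for physical frailty on either scale, so record the one used before the count is made.
4. State no conclusion as an effect in CF beyond what that share supports. Any estimate in the subset should be descriptive only, because the subset may be too small to carry an efficacy claim.

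The cost is wording and one table on existing data. The downside is a narrower claim.

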#### 2.1.4. Study Schedule

In Figure 1, the study schedule of the following trial protocol is shown.

Participants were invited to undergo a face-to-face clinical assessment and neurocognitive batteries. In addition, subjects were asked about their socio-demographic status, their lifestyle, and their diet habits. Body Mass Index (BMI) was calculated too. The Everyday Memory Questionnaire (EMQ) was administrated to evaluate the presence of Subjective Memory Complaints (SMCs), whereas the Cognitive Reserve Index questionnaire (CRI-q) was used to measure cognitive reserve. Symptoms of depression were evaluated with the Geriatric Depression Scale (GDS), whereas physical health in general was estimated by the number of chronic diseases, by the Cumulative Illness Rating Scale (CIRS index), and by the number of drugs. Moreover, functioning skills in daily life were valued through the Barthel Index for Activities of Daily Living (Barthel index), Tinetti, and Instrumental Activities of Daily living (IADL) scales, in order to investigate the functional impact of any cognitive difficulties. Finally, an assessment of physical activity in daily life was performed. 

Specific scales/tools were used to assess the frailty status: the “Italian Frailty Index” (IFI) [31], an Italian version of the frailty index based on the accumulation of age-related deficits; the Frailty Instrument (FIt) for primary care based on the Survey of Health, Aging and Retirement in Europe (SHARE-FIt) [32], valuating five items (i.e., grip strength and four self-reported items: fatigue, loss of appetite and/or eating less than usual, difficulties climbing stairs and/or walking 100 m, and low level of physical activity); and the CDR scale to quantify the severity of symptoms of dementia.

A baseline neuropsychological visit, scheduled within a mean of 20 days of the face-to-face clinical assessment, was administered to all eligible participants, who were then allocated to one of the three intervention groups. A blood sample was collected for biomarker measurement from all subjects. Follow-up neuropsychological visits included (i) a visit 3 months after treatment (T3); (ii) a midpoint visit 9 months after treatment (T9); and (iii) an endpoint visit 15 months after treatment (T15). In each follow up, we collected blood samples for biomarker measurement.

#### 2.1.5. Adaptive Randomization

Subjects were divided into three groups with different levels of cognitive frailty, defined according to tertiles of distribution of the scores of tests for the evaluation of memory skills (Story recall, Rey Auditory Verbal Learning Test—RAVLT immediate and delayed recall, and Rey–Osterrieth Complex Figure—ROCF Recall), attention skills (Trail Making Test part A and part B, TMT-A, TMT-B, Rey–Osterrieth Complex Figure—ROCF copy), and MMSE and GDS scores.

Participants were randomly assigned to the active treatment group (O_2_; O_2_-O_3_) or the placebo group (air), balanced for CF, so that each treatment arm accommodated a similar proportion of subjects in each tertile. The definition of the tertiles of CF was performed at different times, over a period of 12 months, on groups of 12/16 subjects, as enrollment progressed and before starting treatment. Being a double-blind study, both the researchers of the research team and the participants remained blinded to the treatment assignment until the completion of the study, while the medical doctor performing the treatment knew the treatment group, but not tertile of fragility. During recruitment, the medical doctor performing the treatment periodically re-evaluated the size of the treatment subgroups based on the recruitment and dropout rate.

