#### 2.1.12. Statistical Analysis

***Sample size*.** The power analysis was performed by the analysis of the univariate linear regression test. Using the accuracy of the model IFI scale as a multiple partial coefficient (R^2^) and the neuropsychological tests as fixed predictors, we found a power effect of 0.92 related to our population of 76 subjects. Similar findings (power effect of 0.80) were found when we considered the SHARE-Fit scale.

### 2.2. PART 2

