#### 2.2.2. Statistical Analysis

***Data analysis*.** We will present as means and standard deviations the descriptive statistics on cognitive and biological markers in the three treatment groups. The association between categorical variables will be analyzed using the Chi-square test.

The Automatic Linear Modeling (ALM) model that is based on a machine learning approach to find the best predictive model using available data will be used. A set of neuropsychological/biological values will be analyzed as independent input variables, while the scores of IFI or SHARE-FIt scales will be analyzed as continuous output (target) (dependent) variables. Longitudinal comparisons will be performed using univariate analysis, where the clinical parameters relating to the IFI and SHARE-FIt scales will be entered as dependent variables, the significant values obtained from ALM as covariates, and time and treatment as fixed factors. For the metabolomic analysis, PCA analysis (Principal Component Analysis) and a univariate analysis will be performed to evaluate the effects of the treatment on the presence/distribution of the metabolites. 

With the aim to correlate any clinical/cognitive improvements with molecular profiles to identify markers associated with response to treatment, the generalized linear mixed model (GLMM) will be used where the biological values and those relating to neuropsychological tests and the times of follow-up will be analyzed as independent input variables, while the values relating to the IFI or SHARE-FIt scales will be analyzed as weight variables and the treatments as (dependent) variables. “Air treatment” will be used as a comparison variable. All these analyses will be performed using SPSS ver. 29.

Differentially expressed genes will be identified using R-Bioconductor by applying both a fold change and p-value threshold (R-Limma test *p* value < 0.05; |Log2 fold-change ratio| > 1.0). By Fisher’s exact test, we will analyze the categories and functional pathways of upregulated or downregulated genes, using all genes in the array as the “reference” genome, or through the use of Ingenuity Pathway Analysis (IPA, Qiagen, Venlo, The Netherlands) to infer alterations in biological pathways and functions. 

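### Arms were balanced on batch-specific cognitive and mood tertiles that include no frailty scale, and the stated model names no baseline frailty, tertile or batch term

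*Protocol article*

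**What the plan says.** **Allocation (Protocol article, section 2.1.5).** Participants were sorted into three CF levels by tertiles of story recall, RAVLT, ROCF recall and copy, TMT-A and TMT-B, MMSE and GDS, and assignment to O2-O3, O2 or air was balanced on those tertiles. The cut-points were not set once: "The definition of the tertiles of CF was performed at different times, over a period of 12 months, on groups of 12/16 subjects".

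**Control of arm size (same section).** The research team and participants were blinded, "while the medical doctor performing the treatment knew the treatment group, but not tertile of fragility". The section then reports, with no rule attached, that as enrolment went on "the medical doctor performing the treatment periodically re-evaluated the size of the treatment subgroups based on the recruitment and dropout rate".

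**Frailty measures.** Section 2.1.4 lists IFI, SHARE-FIt and CDR as the frailty instruments. Section 2.1.7 makes change from baseline in IFI or SHARE-FIt the primary endpoint. None of the three is an input to the tertiles. The Introduction reports a 2013 consensus view of CF as a "simultaneous state of both cognitive impairment (clinical dementia rating [CDR] = 0.5) and physical frailty (frailty phenotype"), and the Discussion says that frailty/CF was assessed with IFI, SHARE-FIt and CDR.

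**Model (section 2.2.2).** IFI and SHARE-FIt are the dependent variables. The terms are whatever neuropsychological or biological values ALM finds significant, plus "time and treatment as fixed factors". Tertile, enrolment batch and the baseline value of the outcome are not listed.

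**The concern.** There are three connected weaknesses.

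- **The stratification does not enforce balance on the outcome's own baseline.** In a trial of 75 people in three arms, baseline frailty is likely to be the strongest predictor of follow-up frailty. It is neither a stratum nor a named covariate, although it was measured.
- **The allocation factor is not carried into the analysis.** Arms were balanced on tertile within small successive groups, but the model has neither term. The tests behind the tertiles enter only if a data-driven selection step keeps them.
- **Nothing guards against calendar drift.** If the re-evaluation of subgroup sizes led to different ratios in different batches, arm would be associated with time of enrolment, and a model without batch could not separate the two. The article gives no rule and no table from which to judge this.

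The treatment contrast would be less precise than the data allow and open to a chance difference in baseline frailty. In addition, strata described as levels of cognitive frailty do not contain a frailty scale.

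**Working it through.** **Inputs.** From the documents: 75 participants (Abstract and section 2), three arms, batches of 12 to 16. Assumed: equal arms of about 25 (no ratio is stated), two-sided alpha 0.05, 80% power, baseline-to-follow-up correlation r = 0.7.

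**1. The article's own power figure.** Section 2.1.12 says "we found a power effect of 0.92 related to our population of 76 subjects", with 0.80 for SHARE-FIt. This is a regression of the frailty scale on the neuropsychological tests. No R², number of predictors or alpha is given. At N = 76 and alpha 0.05, power 0.92 needs R² between 0.133 (1 predictor) and 0.320 (20 predictors), and power 0.80 needs 0.096 to 0.262. The figures can be neither confirmed nor refuted, and they do not concern the treatment contrast.

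**2. Batch arithmetic.**
- Number of batches: 75/16 = 4.7 to 75/12 = 6.3.
- People per tertile in a batch: 12/3 = 4.0 to 16/3 = 5.3.
- People per tertile-by-arm cell in a batch: 12/9 = 1.3 to 16/9 = 1.8.

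**3. What a tertile means across batches.** Simulating one normal score for 75 people with no drift, 17% to 19% fall in a different tertile by batch cut-points than by pooled cut-points. The same label does not mark the same level in every batch.

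**4. Detectable difference between two arms of 25.** The normal approximation is (1.96 + 0.84) × √(2/25) = 0.79 SD; with the t distribution it is about 0.81 SD.

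| Dependent variable | Multiplier at r = 0.7 | Detectable difference |
|---|---|---|
| Raw follow-up score | 1 | 0.81 SD |
| Change from baseline | √(2(1 − 0.7)) = √0.6 = 0.775 | 0.63 SD |
| Follow-up with baseline as covariate | √(1 − 0.49) = 0.714 | 0.58 SD |

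At r = 0.5 the change and covariate figures are 0.81 and 0.70 SD; at r = 0.8 they are 0.51 and 0.49 SD.

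**5. Chance imbalance.** If baseline frailty is balanced by chance alone, the difference in baseline means between two arms of 25 has standard deviation √(2/25) = 0.28 SD.

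**6. Effect of the omitted terms on error rates.** The simulation used N = 75, five batches of 15, 1:1:1 allocation balanced within tertile and no drift, with 2,500 runs per setting. It assumed a true difference of 0.6 SD, a baseline-to-follow-up correlation of 0.5 or 0.8, and a correlation of 0.2 or 0.6 between tertile score and baseline frailty.

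| Model | Type I error | Power |
|---|---|---|
| Raw follow-up score | 0.031–0.049 | 0.54–0.56 |
| Change score | 0.033–0.049 | 0.54–0.91 |
| Baseline as covariate | 0.042–0.049 | 0.65–0.93 |
| Baseline, tertile and batch | 0.041–0.050 | 0.64–0.93 |

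Leaving out tertile and batch makes the test slightly conservative. Nearly all the gain comes from the baseline covariate; tertile and batch add no power beyond it.

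**The case against.** Much of the case on the other side stands.

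- **Arm sizes changed.** A reader might infer that the unblinded doctor altered the ratio. The text says the sizes were re-evaluated; it reports no change and says the doctor did not know the tertile. A drift bias can be computed only by assuming both a changing ratio and a changing population. Drift in the level of frailty would also largely subtract out of a change-from-baseline endpoint.
- **Arms are unbalanced on frailty.** This does not follow. Assignment was random, so frailty is balanced in expectation. What is missing is enforcement, which matters at 25 per arm.
- **Omitting the allocation factors inflates false positives.** The simulation shows the opposite direction under 1:1:1 allocation.
- **Batch-specific cut-points invalidate the comparison.** They do not. If arms are balanced within each batch's tertiles, the contrast stands, and section 2.2.2 does not analyse by tertile. The shift affects only what the label means.
- **The gain is 0.81 to 0.58 SD.** That takes the raw score as comparator. Section 2.1.7 defines the endpoint as change, for which the gain is 0.63 to 0.58 SD. Section 2.2.2 does not say which is analysed.
- **The trial departs from its own definition of CF.** The Introduction reports a consensus and notes that definitions have changed; the Discussion says a valid operational definition may still be needed. The mismatch is one of labelling.
- **Details may lie elsewhere.** An arm-size rule may be in the full protocol, which is not shown. The model terms, however, are written out in the article.

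**Conclusion.** The point holds in a limited form. The strata contain no frailty scale, their cut-points move between batches, and the stated model secures no adjustment for baseline frailty, tertile or batch. The main loss is precision: at r = 0.7 the detectable difference falls from 0.63 to 0.58 SD if the endpoint is analysed as change, or from 0.81 to 0.58 SD if the raw score is analysed. Chance differences in baseline frailty also go unprotected. The figures assume equal arms of 25 and no dropout.

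The documents do not support reading this as a biased allocation or as an inflated type I error. Batch is worth including as insurance, because the article gives no means of ruling out ratios that changed over time.

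**What to change.** 1. Name baseline IFI (or SHARE-FIt, matching the outcome) as a covariate in the primary model, fixed in advance and not subject to ALM selection. Model the T3, T9 and T15 values as the response, so that T0 is not both covariate and outcome.
2. Include the tertile as allocated, with enrolment batch as a random effect or stratum. Expect little power gain; the terms respect the allocation and protect against calendar drift if ratios did change.
3. Tabulate allocation by batch and arm, and state what rule governed the re-evaluation of subgroup sizes.
4. Describe the strata as batch-specific tertiles of cognitive and mood scores, not as frailty levels.

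Section 2.2.2 is written in the future tense, so these changes are still open. Recruitment is reported as complete, so changing who decides arm size would have little effect now. The cost is a few model terms and one table. Tertile uses 2 degrees of freedom and batch about 4 to 6 if fixed. A random effect avoids most of that, although its variance will be poorly estimated from so few batches.
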